### Randomization and Blinding

Participants will be allocated to intervention and control groups using a uniform 1:1 (control:intervention) allocation ratio and a computer-generated, simple randomization procedure. We will monitor the comparability between groups and, given the large sample size, the groups will be balanced based on three sources of variability with regard to smoking—sex, age, and cigarette consumption [40]. As documented in similar large trials, the likelihood is remote that, by chance, the two study groups may not be well matched for baseline characteristics [41-43]. Owing to the nature of the intervention, participants will be aware of the group to which they have been assigned. However, investigators and data collectors will be blinded to group allocation until completion of the trial.

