### Data Collection

#### Baseline Questionnaire

Baseline data will be collected via a self-administered, online questionnaire completed by all consenting participants in both intervention and control groups. The baseline questionnaire will include the following demographic items: age, sex, ethnicity, marital status, education, income, and employment status. The following variables related to tobacco consumption will also be recorded: current smoking status, amount smoked, number and duration of past quit attempts, intentions to quit in the next 6 months, and the degree of nicotine dependence. Participants will also be asked a series of psychosocial questions, including beliefs and attitudes about quitting, self-efficacy or confidence in quitting, perceived stress and social support, and social norms related to smoking. Furthermore, participants will be asked about experience with mobile phone apps and self-help, use of NRT, and other cessation aids/supports, such as quitlines.

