### Analysis Plan

#### Statistical Analysis

The intention-to-treat principle will be followed for statistical analyses and the imputation method for missing data will be conservative whereby nonresponders will be classified as smokers. Characteristics will be compared between the groups at baseline, at 3-month follow-up, and at 6-month follow-up using independent *t* tests for continuous variables, or chi-square tests for categorical variables as appropriate. Mann-Whitney U tests will be used where data are not normally distributed. Preliminary analyses using models appropriate for the distribution of the variables will be undertaken to determine variables that differ between treatment groups, and between those with complete and incomplete follow-up data. Any variables showing a significant difference will be used in models as covariates to adjust for imbalances between the groups.

The primary response variable—30-day abstinence at 6-month follow-up—will be analyzed in a logistic regression model with the treatment group as the main explanatory variable. Age, sex, and level of addiction will be included, as well as other covariates, to adjust for any differences between the groups. The coefficient for the treatment group will be tested at the 5% level using a likelihood ratio test. Evidence against the null hypothesis that the coefficient is zero will indicate a significant difference between the treatment groups, after adjustment for covariates that differ between the groups.

Secondary analyses that involve comparisons of 7-day abstinence, quit attempts, and consumption levels will be conducted using generalized linear models that consider the distribution of the response variable (eg, Poisson models for numbers of quit attempts) and special features of the data (eg, zero-inflated Poisson models for quit attempts, if necessary). Similarly, variables such as satisfaction, use of e-cigarettes, and use of cessation services will be modeled using generalized linear regression models that include the indicator variable for condition.

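### Cigarette consumption is named as a factor on which the arms should balance, but it enters the primary model only if a significance test selects it

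*Protocol article*

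**What the plan says.** Three parts of the protocol article bear on this.

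- **Randomization and Blinding.** Allocation is made "using a uniform 1:1 (control:intervention) allocation ratio and a computer-generated, simple randomization procedure". No stratification, blocking or minimization is described. The section then states that "given the large sample size, the groups will be balanced based on three sources of variability with regard to smoking—sex, age, and cigarette consumption", adds that comparability will be monitored, and holds that "the likelihood is remote that, by chance, the two study groups may not be well matched for baseline characteristics".
- **Baseline Questionnaire.** Consumption is recorded at baseline ("amount smoked, number and duration of past quit attempts"). Degree of nicotine dependence appears in the same list as a separate item.
- **Statistical Analysis.** For the primary logistic model: "Age, sex, and level of addiction will be included". The sentence goes on to allow further, unnamed covariates where the arms differ. The preceding paragraph gives the selection rule. Preliminary analyses look for variables that differ between the arms, and between participants with complete and incomplete follow-up, and then "Any variables showing a significant difference will be used in models as covariates". In the same section, consumption levels are to be analysed with generalized linear models. No baseline consumption term is named there.

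**The concern.** The two lists do not match. The randomization section picks out sex, age and consumption. The analysis section fixes age, sex and level of addiction. Since the questionnaire treats amount smoked and dependence as separate variables, level of addiction cannot simply be read as another name for consumption.

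Consumption is thus neither controlled by the allocation method nor adjusted for as a named covariate. Its only stated route into the primary model is a significance test on the trial's own data. An imbalance just short of p=.05 is left unadjusted and one just past it is adjusted, so the model behind the primary p-value is not fixed in advance.

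At stake are full prespecification of the primary model and, separately, the precision of the secondary comparison of cigarette consumption, for which baseline consumption is the obvious covariate.

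**Working it through.** **Inputs from the document (Sample Size and Power Calculations).** 677 per arm; abstinence 8.8% in control and 13.6% in intervention after allowing for 20% attrition; two-sided alpha .05; power 80%.

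**Inputs that are assumptions.** One SD of consumption lowers the odds of quitting by 30% to 50%. Baseline and 6-month consumption correlate at 0.5. The document gives neither figure.

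**1. Reproduce the plan's sample size.** Pooled two-proportion formula without continuity correction: n = [1.96·√(2·p̄·q̄) + 0.8416·√(p₁q₁ + p₂q₂)]² / (p₂ − p₁)².
- 11% vs 17%: 524 per arm, as stated.
- 8.8% vs 13.6%: 677 per arm, as stated.

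This is an unadjusted calculation, so adding a covariate does not change it.

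**2. Planned effect on the model's scale.** ln[(0.136/0.864)/(0.088/0.912)] = 0.489. Its standard error at 677 per arm is √[1/(677·0.136) + 1/(677·0.864) + 1/(677·0.088) + 1/(677·0.912)] ≈ 0.176.

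**3. Chance imbalance in one baseline factor.** The standard error of the standardized difference is √(2/677) = 0.054, so the 95% range is ±1.96 × 0.054 = ±0.107 SD. By construction, consumption differs between arms at p<.05 in 5% of trials. Beyond 0.1 SD the probability is 6.6%, beyond 0.15 SD 0.6%, and beyond 0.2 SD 0.02%.

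**4. Largest shift left unadjusted.** The selection rule is triggered at about 0.107 SD, so that is the largest between-arm imbalance it leaves alone.
- 30% lower odds per SD: 0.107 × ln(1/0.7) = 0.107 × 0.357 = 0.038.
- 50% lower odds per SD: 0.107 × ln 2 = 0.107 × 0.693 = 0.074.
- Against 0.489 this is 8% to 15%. Against the standard error of 0.176 it is 0.2 to 0.4 standard errors.

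**5. Typical shift.** The mean absolute imbalance is 0.798 × 0.054 = 0.043 SD, which gives a shift of 0.015 to 0.030, or 3% to 6% of 0.489. Steps 4 and 5 ignore level of addiction. To the extent that it correlates with consumption, adjusting for it absorbs part of the shift.

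**6. Effect on the primary test.** Simulated likelihood ratio tests with 1354 participants and 1000 runs per scenario. Addiction is in both models (odds ratio 0.7 per SD, assumed), and consumption is added in the second.

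| Assumed consumption OR per SD; correlation with addiction | Type I error without / with consumption | Power without / with consumption |
|---|---|---|
| 0.7; 0.5 | 0.058 / 0.056 | 0.825 / 0.827 |
| 0.8; 0.7 | 0.052 / 0.050 | 0.825 / 0.821 |

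The simulation standard error of each power figure is about √(0.82·0.18/1000) = 0.012, so no difference is detectable. The simulation compares two fixed models and does not imitate the selection rule.

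**7. Consumption outcome.** In a linear model with a baseline correlation of 0.5, residual variance falls to 1 − 0.5² = 0.75 of that in an unadjusted analysis of the 6-month level, a reduction of 25%.

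**The case against.** The strongest reply is that the plan does not exclude consumption. The covariate sentence goes on to admit other covariates, and the rule brings in any variable that differs significantly. A reader who stops at the three named covariates might infer that consumption is left out of the primary model. The full sentence does not support that: inclusion is conditional. This part of the objection stands. What remains is that the condition is a test on the trial data.

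A reader might also infer that simple randomization contradicts a promised balance. It does not. The section predicts balance from the sample size and describes no restricted scheme. Its confidence is also largely justified for big imbalances, given 0.02% beyond 0.2 SD. Only the flat future tense is too strong.

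A third inference would be that omitting consumption distorts the primary test or costs it power. Steps 4 to 6 do not support this. Nor would it be right to count the chance that any of the three named factors differs, because age and sex are already in the model. Only consumption is open, and when it differs at p<.05 the rule adds it.

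Finally, the article does not define level of addiction, so the measure may already contain cigarettes per day. Its definition, and the covariates for a secondary outcome, can properly be left to a fuller document. Neither is counted as an omission here. The mismatch between two lists that the article does state, and the stated selection rule, remain.

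**Conclusion.** The point holds as a minor one. Consumption is named as a factor for balance, is not a fixed covariate, and enters the primary model only through a data-driven rule. The consequence for the primary comparison is small: at most about 0.04-0.07 on the log odds ratio, under the assumed 30-50% reduction in odds per SD and before any allowance for correlation with addiction. The simulated type I error and power do not change detectably.

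The case for changing the plan therefore rests on consistency between its sections, on a primary model fixed in advance, and on better precision for the consumption outcome. The 25% figure for that outcome depends on the assumed correlation of 0.5 and would be smaller or larger with a weaker or stronger one.

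**What to change.** - **Primary model.** Prespecify age, sex, level of addiction and baseline cigarettes per day as covariates, whatever any significance test shows. State how level of addiction is measured. If the scale already contains cigarettes per day, use its remaining items plus cigarettes per day.
- **Consumption outcome.** Adjust 6-month consumption for baseline cigarettes per day.
- **Wording.** Replace the statement that "the groups will be balanced based on three sources of variability with regard to smoking" with one saying that balance is expected on average under simple randomization and that remaining imbalance in the prespecified covariates is handled by adjustment.

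The cost is one covariate that is already collected and a few sentences of text. The randomization and the 677 per arm stay as they are.

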The Preacher and Hayes bootstrapping method will be used to provide point estimates and confidence intervals to assess the significance or nonsignificance of a mediation effect, as it provides an increase in power and does not require the normality assumption to be met [72]. The mediation analyses will proceed by first estimating the difference in the outcome variable between the treatment and control groups, adjusting for age and sex as necessary, and then estimating the difference between the conditions for the mediating variables using bootstrapping. Finally, mediating variables and the treatment group indicator, along with covariates, will be entered into models for the primary and secondary responses. This will allow for an investigation of the role the mediators play in accounting for the differences between conditions. For example, use of e-cigarettes, higher levels of dependence, lower levels of self-efficacy, and low perceived social support might mediate quit success, for example, lower quit rates (see Figure 3). Additional secondary analyses will look at models for the response variables involving a treatment group indicator, covariates, and interactions between covariates and the treatment group indicator. These models will examine whether the relationships between the outcome and covariates differ between the conditions. They will also help to identify potential mechanisms, for example, frequency of app usage, by which the intervention might be operating. Statistical analyses will be performed using SAS version 9.4.

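### The mediator-to-abstinence models choose covariates by a rule aimed at arm imbalance and follow-up completeness, with no commitment to the mediator's baseline value, so the indirect effects may be confounded (secondary aim only)

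*Protocol article*

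**What the plan says.** All references are to the Protocol article. Its Statistical Analysis section sets out mediation in three steps.

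- **Step 1, treatment to outcome:** "first estimating the difference in the outcome variable between the treatment and control groups, adjusting for age and sex as necessary".
- **Step 2, treatment to mediator:** the same sentence runs on from the closing clause of step 1, "adjusting for age and sex as necessary, and then estimating the difference between the conditions for the mediating variables using bootstrapping".
- **Step 3, mediator to outcome:** "Finally, mediating variables and the treatment group indicator, along with covariates, will be entered into models for the primary and secondary responses". The covariates are not listed here.

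The same section says earlier how covariates are chosen. For the primary model: "Age, sex, and level of addiction will be included, as well as other covariates, to adjust for any differences between the groups". In general, after screening for variables that differ between arms, or between participants with complete and incomplete follow-up: "Any variables showing a significant difference will be used in models as covariates to adjust for imbalances between the groups".

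The Baseline Questionnaire section collects "beliefs and attitudes about quitting, self-efficacy or confidence in quitting, perceived stress and social support, and social norms related to smoking". It also collects quit intentions and degree of nicotine dependence. Study Aims lists these psychosocial variables and quit intentions among the mediators, together with frequency of app use, use of cessation services and nicotine withdrawal.

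**The concern.** Steps 1 and 2 compare randomized arms. Step 3 does not: participants are not randomized to a level of self-efficacy or social support at follow-up. Someone who starts with high self-efficacy is likely to score high later and may also be more likely to quit, whether or not later self-efficacy does anything. Baseline self-efficacy then confounds step 3 even if it is perfectly balanced between arms.

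The stated covariate rule does not look for such variables. Under simple randomization, and taking a 5% screening level (the protocol does not give one), a given baseline variable differs significantly between arms in about 5% of trials. The completeness route can admit others, but it selects predictors of dropout, not common causes of mediator and abstinence.

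At stake is the trial's explanation of its result. The Introduction puts particular weight on learning why apps work or fail, and the Discussion expects the sample to show which factors mediate quitting. Bootstrap intervals deal with sampling error and cannot remove confounding.

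**Working it through.** **Protocol figures.** The protocol gives no figure for the mediation analysis. Its sample sizes reproduce with the pooled two-sided formula n = [1.960·√(2p̄q̄) + 0.842·√(p₁q₁ + p₂q₂)]² / d².
- 11% v 17%: (0.962 + 0.411)² / 0.06² gives 524 per group.
- 8.8% v 13.6%: (0.874 + 0.374)² / 0.048² gives 677 per group.

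They serve here only to set N: 1354 randomized, and 1354 × 0.8 = 1083 responders at the planned 20% attrition.

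**Assumed inputs** (the protocol gives none):
- True effect of the follow-up mediator on abstinence: zero.
- Baseline-to-follow-up correlation of the mediator: 0.5.
- Log-odds of abstinence per SD of baseline mediator: g = 0.1, 0.3 or 0.5.
- Shift in the mediator due to the app: a = 0, 0.2 or 0.3 SD.

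**By hand, baseline mediator left out.** The follow-up mediator picks up a spurious coefficient of about 0.5g. Mean abstinence among responders is (11% + 17%)/2 = 14%, so its standard error is about 1/√(1083 × 0.14 × 0.86) = 0.0876. The standard error of the arm shift is about 2/√1083 = 0.0608 SD. A false indirect effect needs both paths to be significant.

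| g | spurious coefficient / SE | chance mediator path is significant | joint, a = 0.2 (shift detected 0.91) | joint, a = 0.3 (shift detected ≈1.00) |
|---|---|---|---|---|
| 0.1 | 0.05/0.0876 = 0.57 | 0.09 | 0.08 | 0.09 |
| 0.3 | 0.15/0.0876 = 1.71 | 0.40 | 0.37 | 0.40 |
| 0.5 | 0.25/0.0876 = 2.85 | 0.81 | 0.74 | 0.81 |

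With the baseline mediator included, the spurious coefficient is zero and the joint chance is about 0.05 × 0.91 to 0.05 × 1.00, or 5%. With a = 0 and the baseline mediator left out, it is at most 0.05 × 0.81 = 4%.

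**By simulation, 1083 responders, addiction already adjusted.** False significant indirect effects appear in about 8% of trials at g = 0.1, about 36% at g = 0.3 and up to about 78% at g = 0.5, for a = 0.2 to 0.3. With the baseline mediator added the figure is about 5%. This agrees with the hand calculation.

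**By simulation, all 1354, addiction as a second confounder.** The follow-up mediator depends on its baseline value (0.5) and on addiction (−0.2), and the baseline mediator is also related to addiction (−0.3). The baseline mediator and addiction each shift the log-odds of abstinence by 0.3 to 0.5 per SD. There were 1000 runs per scenario.

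| Adjusters | a = 0.2 to 0.3 | a = 0 |
|---|---|---|
| Age, sex | 85% to 100% | about 5% |
| Age, sex, addiction | 40% to 85% | 2% to 5% |
| Age, sex, addiction, baseline mediator | 4% to 6% | under 1% |

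Check on the middle row: given addiction, the spurious coefficient should be g × (0.5 × 0.91)/(0.25 × 0.91 + 0.5625) = 0.576g. That is 0.17 at g = 0.3 and 0.29 at g = 0.5, as the simulation found.

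Both simulations used a Monte Carlo interval for the product of the two coefficients in place of the bootstrap.

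**The case against.** Several stronger readings are tempting, and the protocol does not support them.

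- **That mediation adjusts only for age and sex.** That clause belongs to step 1, a randomized contrast. Step 3 has its own unlisted covariates.
- **That addiction is left out.** If step 3 follows the primary model's covariates, addiction is included; otherwise the set is simply unspecified. The point does not depend on this, because the inflation remains with addiction adjusted.
- **That a baseline value exists for every mediator.** Frequency of app use cannot have one, and nicotine withdrawal is named only in the 3- and 6-month questionnaire.
- **That step 1 must reproduce the primary estimate.** Steps 1 and 2 are randomized contrasts, and different covariates there do not create the confounding described. Adding baseline mediators to the total-effect model would itself move that estimate away from the primary one.

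The strongest objection is that a journal article may leave exact covariate lists to a statistical analysis plan, and that covariates could include baseline mediators. This has force: nothing excludes them. But the article is not merely silent. It states a selection rule, and that rule does not suit step 3. It is also fair that every confounding input is assumed, that all scenarios set the true mediator effect to zero, and that the size varies widely with the inputs.

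**Conclusion.** The point stands as an almost free improvement to a secondary aim. As written, the mediator-to-abstinence path may be confounded; a reader might infer that it is confounded, or that any reported mechanism would be false, and the documents do not show that. The size depends on how strongly the baseline mediator predicts abstinence. With addiction adjusted, 1083 responders and a shift of 0.2 to 0.3 SD, false mediation runs from about 8% (log-odds 0.1 per SD) to about 78% (0.5 per SD), against about 5% with the baseline mediator included. If the app does not move the mediator, the rate stays at or below about 5% either way. The primary test and the sample size of 1354 are not touched.

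**What to change.** In the mediation paragraph of Statistical Analysis, add: *The mediator model and the outcome model containing the mediator will both adjust for the baseline value of that mediator where it was collected, and for age, sex and baseline level of addiction, regardless of differences between arms. Indirect effects are interpreted on the assumption of no remaining unmeasured confounding between mediator and outcome.*

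Frequency of app use is exempt, as is withdrawal unless it was measured at baseline. The word baseline matters for addiction because the same section also names dependence as a possible mediator. The randomized total-effect step needs no change.

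The cost is one or two model terms from a questionnaire already in use, and a rule for missing baseline items. No new data are needed.

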### Sample Size and Power Calculations

Sample size calculations are based on a superiority trial [66,67] and are focused on the difference in the objective measure of the primary outcome event—30-day point prevalence abstinence from smoking—between intervention and control groups. Assuming a ratio of 1:1 for intervention to control subjects, an alpha of .05, power of 80%, and an effect size equal to a 50% increase in self-reported abstinence—17% in the intervention versus 11% in the control condition—the required sample size is 524 per group, for a total of 1048 participants using a two-tailed test on proportions [68]. The 50% increase in effect is reasonable and conservative based on trials of interventions using other mobile and Web-based technologies [41,69,70]. The estimated 11% abstinence rate in the control condition is based on the Ontario Tobacco Survey young adult smokers cohort study where in a sample of 592 young adult smokers, 68 (11.5%) were abstinent at the 6-month follow-up [71]. The 11% abstinence rate is what is expected to occur with a standard self-help condition and is similar to other trials that have tested the effect of self-help materials, with validated 6-month cessation rates of 5% to 15% [50,51]. Based on the experience of similar interventions [41,69], an overall estimate of 20% attrition translates into quit rates of 8.8% in the control condition and 13.6% in the intervention. Therefore, the total sample size required for each group is 677, for a total of 1354 participants.

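### The nonresponder-as-smoker rule carries over into the mediation models, where it can make attrition look like mediation or suppression

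*Protocol article*

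**What the plan says.** All places are in the Protocol article.

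- **Missing data (Statistical Analysis).** The analyses follow intention-to-treat, and one imputation rule is given: "the imputation method for missing data will be conservative whereby nonresponders will be classified as smokers".
- **Attrition (Sample Size and Power Calculations).** The same rule is built into the sample size: "an overall estimate of 20% attrition translates into quit rates of 8.8% in the control condition and 13.6% in the intervention".
- **Mediation (Statistical Analysis).** The sequence starts by "first estimating the difference in the outcome variable between the treatment and control groups", goes on to the arm difference in the mediators, and ends thus: "Finally, mediating variables and the treatment group indicator, along with covariates, will be entered into models for the primary and secondary responses". Point estimates and intervals for the mediation effect come from the Preacher and Hayes bootstrap.
- **Mediators (Study Aims).** They are frequency of app use, use of cessation services, quit intentions, nicotine withdrawal and a set of psychosocial variables.
- **Source of mediators.** Apart from app use, these come from the 3- and 6-month online questionnaires (Questionnaire for 3- and 6-Month Follow-Up). App use is also logged per user with time stamps (Process Measures).

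**The concern.** Scoring nonresponders as smokers is a convention for the outcome of a two-arm comparison. It supplies a smoking status but no self-efficacy, withdrawal or support score. The mediation models need both. Because they are models for the primary and secondary responses, they inherit the imputed outcome, and one of two problems follows.

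1. **Mediator from the visit that was missed.** Nonresponders drop out of any model that contains the mediator but stay in the total effect. The change in the treatment coefficient then reflects both mediation and the removal of imputed smokers.
2. **Mediator from 3 months or from the app log.** Nonresponders at 6 months have a mediator value and stay in, all coded as smoking. Any mediator related to answering the 6-month survey becomes related to the coded outcome, even if it has no bearing on quitting.

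Mediation is a named secondary aim, and the Background says that learning why apps do or do not work matters more than whether they work. A spurious mediator would mislead later app design.

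**Working it through.** **1. The plan's own figures.** For two proportions with pooled variance under the null, n per group = [1.960·√(2p̄q̄) + 0.842·√(p₁q₁ + p₀q₀)]² / (p₁ − p₀)².

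- 17% vs 11%: (0.9618 + 0.4115)² / 0.0036 = 523.8, so 524, as stated.
- 13.6% vs 8.8%: (0.8741 + 0.3743)² / 0.002304 = 676.4, so 677, as stated.

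The diluted rates are 0.80 × 17% and 0.80 × 11%, so the plan applies 20% attrition equally to both arms. Expected 6-month nonresponders are 0.20 × 1354 ≈ 271, leaving about 1083 with questionnaire mediators from that visit.

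**2. Total effect in all randomized, direct effect in responders.** Take an inert mediator and the plan's 17% vs 11% among responders.

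- Responders: c′ = logit(0.17) − logit(0.11) = 0.505 (OR 1.66). An inert mediator leaves this unchanged.
- All randomized, attrition a₁ (app) and a₀ (control): c = logit[0.17(1 − a₁)] − logit[0.11(1 − a₀)].
- Apparent share mediated = (c − c′)/c.

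| Attrition app/control | Quit rates, all randomized | c | c − c′ | Apparent share |
|---|---|---|---|---|
| 20%/20% (plan) | 13.60% vs 8.80% | 0.489 | −0.016 | −3% |
| 18%/22% (assumed) | 13.94% vs 8.58% | 0.546 | +0.041 | +7% |
| 15%/25% (assumed) | 14.45% vs 8.25% | 0.630 | +0.125 | +20% |
| 22%/18% (assumed) | 13.26% vs 9.02% | 0.433 | −0.072 | −17% |
| 25%/15% (assumed) | 12.75% vs 9.35% | 0.348 | −0.157 | −45% |

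With equal attrition the factor (1 − a) cancels from the numerators of the two odds, which is why so little is left. With unequal attrition it does not cancel.

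In simulation (677 per arm, 150 trials, 120 bootstrap resamples), the interval for c − c′ across the two sets excluded zero in 97% of trials at 15% app/25% control, and in 9% at 20%/20%. When c and c′ were both fitted in responders, they agreed to within 0.001 (0.520 vs 0.521 at 20%/20%). The product a·b estimated in responders was significant in only 0% to 3% of trials.

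**3. Mediator observed, nonresponders kept in as smokers.** Assumptions:

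- a continuous mediator measured in both arms, with no effect on quitting;
- shifted 0.4 SD by the app;
- predicting 6-month response with log OR 0.3, 0.5 or 0.8 per SD;
- 20% attrition overall and 17% vs 11% true quit rates.

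The false mediator coefficient is from a very large sample. The error rates are for 677 per arm (300 trials, 200 resamples), and the ranges span repeated runs.

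| Log OR for response, per SD | False mediator coefficient, smoker scoring | False-positive a·b, smoker scoring | False-positive a·b, responders only |
|---|---|---|---|
| 0.3 | 0.07 | 14–16% | 5–7% |
| 0.5 | 0.11 | 26–28% | 6% |
| 0.8 | 0.16 | 48–52% | 6% |

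In responders the mediator coefficient is about zero throughout. At log OR 0.5 the arms' attrition differs by only about 3 points, a gap produced by the mediator itself. The false indirect effect is 0.4 × 0.106 = 0.042, about 8% of the total log OR of 0.53.

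**The case against.** The strongest reply is that the article does not say who enters each mediation step, which visit supplies the mediator, or how a missing mediator is handled. Those details commonly sit in an analysis plan, which is not shown here, so silence on them is no fault. This stands. A reader might infer that the plan definitely uses different people in successive steps, but the text does not say so, and a single responder set for all steps is compatible with it. What remains is a stated rule: intention-to-treat with smoker scoring is set out for the statistical analyses generally, with no exception for mediation.

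A reader might also infer that the planned 20% attrition by itself produces false mediation. It does not: at equal attrition the first artefact is −3%, and the article gives no arm-specific figures.

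Nor do all mediators depend on a questionnaire answered at 6 months. App use is logged and 3-month answers may exist. Those cases escape the first problem but fall under the second.

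The bootstrap of a·b is the named test, and estimated in responders it is not inflated. Estimated with nonresponders scored as smokers, as the general rule implies, it is.

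The plan also compares complete with incomplete follow-up and adjusts for variables that differ. This helps, but it supplies no mediator value and does not undo the outcome coding.

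Finally, a responder-only analysis conditions on an event after randomization and can itself be biased if response depends on both mediator and quitting. That limits its use as a remedy.

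**Conclusion.** The concern holds in a limited form: the general missing-data rule, carried into the mediation models, is unsuitable there. The first artefact is negligible under the plan's equal attrition. It becomes material only if attrition differs by arm and the total and direct effects come from different sets. The +20% and −45% figures rest on an assumed 10-point gap, and a 4-point gap gives +7% or −17%. The second artefact needs no imposed attrition gap, but it does need a mediator that the app shifts and that predicts survey response. The 14% to 50% false-positive range rests on the assumed 0.4 SD shift and log ORs of 0.3 to 0.8. For logged app use the same mechanism applies if use predicts response, but its size was not computed. The primary test and both stated sample sizes are unaffected. This should be changed because it bears on a named aim and the remedy is cheap.

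**What to change.** Add to the mediation paragraph of Statistical Analysis:

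- All mediation steps, including the total effect, use one common analysis set. The preferred set is all randomized participants, with mediator and outcome multiply imputed together within arm from baseline and 3-month data.
- Participants with both mediator and smoking status observed are analysed as a sensitivity analysis, with a note that this conditions on response.
- The nonresponder-as-smoker score is kept for the primary test and used in mediation at most as a sensitivity analysis.
- Attrition is reported by arm.

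The cost is a few sentences and some programming to combine imputation with the bootstrap. The imputation assumes that baseline and 3-month data explain who responds at 6 months, which should be stated. The total effect in the mediation report will differ slightly from the primary estimate, and the report must say why.
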